 Only on day 0/1/2 and 42/43/44

 Full chemistry panel at screening and follow-up, short panel for all other samples

 Only at day pre-first-dose and after exercise test on 39/40/41/42 and before exercise test on 46/47/48/49

 Only at day 0/1/2 post-dose, 1-3h

 Not at Time to Exhaustion test, except for Blood sample chemistry

 Height measured at screening only

 Before and after exercise test on day 39/40/41/42

 Before and after Time to exhaustion test on day 46/47/48/49

**Table 2.** Exercise parameters in endurance performance.

| Abbreviation        | Description                                                                     | Calculations / Characteristics                                                                                                                                                                                        |
|---------------------|---------------------------------------------------------------------------------|-----------------------------------------------------------------------------------------------------------------------------------------------------------------------------------------------------------------------|
| $V_{O2, \max}$      | Maximal oxygen consumption ( $\text{ml kg}^{-1} \text{ min}^{-1}$ )             |                                                                                                                                                                                                                       |
| $P_{\max}$          | Maximal power output (W)                                                        | $1\text{W} = 1\text{J/sec}$                                                                                                                                                                                           |
| $V_E$               | Respiratory minute ventilation (L/min)                                          |                                                                                                                                                                                                                       |
| $V_t$               | Tidal volume (L)                                                                |                                                                                                                                                                                                                       |
| $R_f$               | Respiratory frequency                                                           |                                                                                                                                                                                                                       |
| $V_{O2}$            | Oxygen consumption (L/min)                                                      |                                                                                                                                                                                                                       |
| $V_{CO2}$           | Carbon dioxide production (L/min)                                               |                                                                                                                                                                                                                       |
| $eqV_{O2}$          | Ventilatory equivalent for oxygen                                               | $V_E/V_{O2}$                                                                                                                                                                                                          |
| $eqV_{CO2}$         | Ventilatory equivalent for carbon dioxide                                       | $V_E/V_{CO2}$                                                                                                                                                                                                         |
| EE                  | Energy Expenditure (J/sec)                                                      | $([3.869 \times V_{O2}] + [1.195 \times V_{CO2}]) \times (4.186/60) \times 1000$                                                                                                                                      |
| GE                  | Gross Efficiency (%)                                                            | Reflects the percentage of total chemical energy expended that contributes to external work, with the remaining energy lost as heat.
$(\text{Work rate (J/sec)} / \text{Energy Expenditure (J/sec)}) \times 100\%$ |
| DE                  | Delta Efficiency (%)                                                            | $(\Delta \text{ Work Production (J/sec)} / \Delta \text{ Energy Expenditure (J/sec)}) \times 100\%$                                                                                                                   |
| CE                  | Cycling economy ( $\text{W L}^{-1} \text{ min}^{-1}$ )                          | Can be defined as the submaximal $V_{O2}$ per unit of body weight required to perform a given task.
$P/V_{O2}$                                                                                                     |
| $\text{Fat}_{\max}$ | The highest absolute fat oxidation                                              |                                                                                                                                                                                                                       |
| LT1 = AT = OBLA     | Lactate Threshold 1 = Anaerobic Threshold = Onset of Blood Lactate Accumulation | The threshold where blood lactate levels raise 1mmol/L above baseline values.                                                                                                                                         |
| LT2                 | Lactate Threshold 2                                                             | The highest exercise intensity where lactate levels remain stable.                                                                                                                                                    |
| VT1                 | Ventilatory Threshold 1                                                         | The first increase in $V_E$ that is proportional to the increase in $V_{CO2}$ with no increase in $V_{O2}$ . Increase of end tidal $O_2$ pressure.                                                                    |
| VT2 = RCP           | Ventilatory Threshold 2 = Respiratory Compensation Point                        | Represents itself at a high work.
$V_E$ increases far more compared to $V_{CO2}$ .
End tidal $CO_2$ pressure decreases.                                                                                         |

## 1 BACKGROUND AND RATIONALE

### 1.1 Context

#### 1.1.1 Need for research on doping

A recent report of the Union Cycliste Internationale (UCI) gives an in-depth analysis of doping throughout cycling's history, from 1890 to the present day. The report's final conclusion is that cycling has had, and continues to have, a serious doping problem.

Although it could be argued that administering substances that improve performance is forbidden and nothing more needs to be known about it, research to investigate the effects and safety of doping substances in this population is necessary. There are number of reasons for this. First, it is often unknown if a forbidden substance really enhances performance. If this is not the case the need for administration is strongly diminished. Additionally the adverse effects of such substances are often insufficiently known and athletes may be exposed to risks without being adequately informed about them.

#### 1.1.2 Erythropoietin substances in patients and athletes

Recombinant Human Erythropoietin (rHuEPO) is used to treat patients with anemia resulting from chronic kidney disease. The correction of the anemia results in an increase in exercise capacity in these patients. The treatment immediately attracted the attention of athletes because they assumed that rHuEPO would also improve their exercise performance. Due to this presumption, the use of rHuEPO in athletes became very common. In 1990, the use of rHuEPO was placed on the list of prohibited substances published by the World Anti-Doping Agency (WADA). At the time of the first ban there was no published evidence that rHuEPO would actually improve sports performance.

#### 1.1.3 Examination of the evidence for the ergogenic properties of rHuEPO in cyclists

The evidence for the effect of rHuEPO in well trained athletes is in fact sparse until today. A qualitative systematic review of the available literature was performed in 2012 to examine the evidence for the performance enhancing properties of rHuEPO in cyclists.

The review demonstrated that the characteristics of the study populations differed from the population suspected of rHuEPO abuse. rHuEPO studies often used untrained or moderately trained cyclists. It cannot be assumed that effects found in these studies automatically apply to well-trained cyclists. Most studies used a small number of untrained subjects and the quality of the research was often questionable. In these studies, the main studied effect was the maximal oxygen carrying capacity of blood ( $V_{O2, max}$ ) which only has a remote connection to performance in endurance sports, especially in well-trained athletes. This is in line with the knowledge that multiple factors affect performance, in which oxygen carrying capacity of the blood becomes less relevant when other factors become rate-limiting. Endurance performance may be better correlated with submaximal exercise factors. There a number of findings that support this last notion. Firstly, research into training for endurance performance shows that moderately trained athletes are able to improve  $V_{O2, max}$  by interval and/or intensive training, whereas these training regimens do not improve  $V_{O2, max}$  in well-trained athletes. After initial years of training, these well-trained athletes maintain a plateau in their  $V_{O2, max}$ , but continue to improve their performance. This shows that other factors have to play an important role in endurance performance.

Secondly, long exercise times during consecutive days, with the finish line as a known end-point (contrary to the 'open end' of time-to-exhaustion tests) makes it crucial for cyclists to distribute their power during a race. This, combined with (team) tactics, the terrain and the effects of drag force, means that cyclists work for only a small amount of time at their peak intensities ( $V_{O2, max}$ ), the rest of the time they will work at sub-maximal intensities where submaximal exercise factors are more important.

Finally, adverse events were never studied despite the fact that there is much evidence from patient studies that rHuEPO may cause hypertension and thrombotic events. Uncontrolled use of rHuEPO therefore involves risks for the users' health, irrespective of such a substance being used legally or illegally.

#### **1.1.4 Study objectives**

The current study will

- explore the effects of NeoRecormon on cycling performance in well-trained cyclists by
  - performance in *exercise tests*
  - performance in a *competition*
  - measuring markers from the haematological module of the *Athlete Biological Passport*
  - measuring *blood flow*
- evaluate the safety of NeoRecormon in well-trained cyclists.
- evaluate the performance of doping detection methods for NeoRecormon use in well-trained cyclists.

## **1.2 Non-clinical information**

### **1.2.1 Non-clinical pharmacology**

Please refer to the respective Summary of Product Characteristics (SmPC) (see appendix 1) and European Public Assessment Report (EPAR) (see appendix 3).

### **1.2.2 Non-clinical pharmacokinetics and metabolism**

Please refer to the respective SmPC and EPAR (see appendix 1 and 3).

### **1.2.3 Non-clinical toxicology and safety pharmacology**

Please refer to the respective SmPC and EPAR (see appendix 1 and 3).

## **1.3 Clinical information**

### **1.3.1 Clinical pharmacology**

Please refer to the respective SmPC and EPAR (see appendix 1 and 3).

### **1.3.2 Clinical pharmacokinetics and metabolism**

Please refer to the respective SmPC and EPAR (see appendix 1 and 3).

### **1.3.3 Clinical toxicology and safety pharmacology**

Please refer to the respective SmPC and EPAR (see appendix 1 and 3).

## **1.4 Study rationale**

### **1.4.1 Benefit and risk assessment**

NeoRecormon is a registered drug. The safety profile of this compound is known. Because side effects might occur and anaphylactoid reactions were observed in isolated cases ( $\leq 1/10.000$ ) (see SmPC, appendix 1), the study drug administrations will be done in the clinic under medical supervision. Subjects will be closely monitored and will only be discharged from the unit if their medical condition allows this.

Subjects will receive a dose of 2000, 5000 or  $\geq 6000$  IU with a maximum of 10.000 IU/week of NeoRecormon once a week for 8 weeks. The dosage depends on haemoglobin (Hb) concentration

and haematocrit (Ht) measured prior to administration. If Ht is  $\geq 52\%$  dosage will be interrupted. If Ht is  $< 52\%$  the dosage depends on the Hb concentration (see Figure 1).

The effects of NeoRecormon used in patients in an autologous blood predonation programme most closely resembles the effects of NeoRecormon in healthy volunteers. For the use of NeoRecormon in an autologous blood predonation programme, the SmPC (see appendix 1) states that the maximum dose should not exceed 1200IU/kg (or 90.000 IU for a 75kg subject) per week for subcutaneous administration. Planned doses of 2000IU, 5000IU or  $\geq 6000$  IU with a maximum of 10.000IU/week of NeoRecormon will be well below this maximum dose and are therefore considered safe. The risk is considered small and therefore acceptable compared to the scientific benefit.

#### 1.4.2 Medical and regulatory background

The genetically engineered erythropoietin hormone, rHuEPO (in this research NeoRecormon), works in the same way as the natural hormone erythropoietin (EPO). EPO is a (glycoprotein) hormone primarily produced by the kidneys. The kidneys secrete EPO in response to hypoxia in the renal circulation. The secreted EPO binds to the EPO receptor on the erythroid progenitor cell surface and in this way activates intracellular signaling pathways that lead to erythropoiesis in the bone marrow. Erythropoiesis is the proliferation and differentiation of erythroid progenitor cells to erythrocytes (red blood cells). Erythrocytes are responsible for oxygen transport through the blood. Due to the lack of a nucleus and other cellular machinery, erythrocytes are not able to repair themselves. They have a lifespan of approximately 120 days in the circulation after which they are degraded by the spleen (2-3 million every second). To keep the oxygen carrying capacity of the blood at a steady level, constant erythropoiesis is necessary. The concentration of EPO in blood is relatively constant at approximately 5 pmol L.

#### 1.4.3 Study population

Forty-eight well-trained male subjects, 18 to 50 years of age who have a Hb level  $> 8.0$  mmol/L and  $\leq 9.8$  mmol/L, a Ht  $< 48\%$  and a maximal power output  $> 4.0$  W/kg will be included.

Previous studies showed that professional cyclists have Hb concentrations between 8.25 and 10.25 mmol/l and Ht levels between 39.2 and 48.1%. The normal Hb concentration for males is 8.75 to 11.25 mmol/l. The rHuEPO treatment in this study will increase Hb levels of the subjects with 10-15%. Subjects will be excluded during the screening when they have Hb levels  $> 9.8$  mmol/l, because the normal Hb level (11.25 mmol/l) should not be exceeded ( $9.8 \times 1.15 = 11.27$  mmol/l).

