##### ***Dosage Rationale***

An initial dose of 5000IU/week will be administered because previous studies showed that with this dose the above mentioned target range should be reached. If the upper limit of the target range is exceeded the dose will be interrupted until the Hb concentration falls back into the range. At that point, therapy should be restarted at 2000IU/week. If treatment weeks  $\geq 5$  and  $Hb < (1.10 \times \text{Initial Hb})$  the dose will be adjusted to  $\geq 6000$  IU/week (maximal 10.000IU/week), so that it is still possible to reach the target range within 8 weeks.

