### 4.3 Exclusion criteria

Eligible subjects must meet none of the following exclusion criteria:

- ❖ Any clinically significant abnormality, as determined by medical history taking and physical examinations, obtained during the screening visit that in the opinion of the investigator would interfere with the study objectives or compromise subject safety.
- ❖ Unacceptable known concomitant diagnoses or diseases at baseline, e.g., known cardiovascular, pulmonary, muscle, metabolic or haematological disease, renal or liver dysfunction, ECG or laboratory abnormalities, etc.
- ❖ Unacceptable concomitant medications at baseline, e.g., drugs known or likely to interact with the study drugs or study assessments.
- ❖ Unacceptable potential cycling performance enhancing medications at baseline, e.g. Erythropoiesis-stimulating agents, Anabolic Androgenic Steroids, Growth Hormone, Insulin, IGF-I and Beta-Adrenergic Agents.
- ❖ Blood transfusion in the past three months.
- ❖ Loss or donation of blood over 500 mL within three months.
- ❖ Participation in a clinical trial within 90 days of screening or more than 4 times in the previous year.
- ❖ Known hypersensitivity to the treatment or drugs of the same class, or any of their excipients.
- ❖ Any known factor, condition, or disease that might interfere with treatment compliance, study conduct or interpretation of the results such as drug or alcohol dependence or psychiatric disease.
- ❖ Positive urine drug test at screening.
- ❖ Positive alcohol breath test at screening.
- ❖ Haemoglobin (Hb) concentration  $> 9.8$  mmol/l at screening.
- ❖ Hb concentration  $< 8$  mmol/l at screening.
- ❖ Haematocrit (Ht)  $\geq 48\%$  at screening.

- ❖ Being subject to WADA's anti-doping rules, meaning being a member of an official cycling union or other sports union for competition (such as the KNUU) or participating in official competition during the study.
- ❖ Positive results from serology at screening (except for vaccinated subjects or subjects with past but resolved hepatitis)
- ❖ Previous history of fainting, collapse, syncope, orthostatic hypotension, or vasovagal reactions.
- ❖ Any circumstances or conditions, which, in the opinion of the investigator, may affect full participation in the study or compliance with the protocol.

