## **6.2 Safety endpoints**

*Safety measurements before NeoRecormon/placebo administration*

Safety will be assessed by:

- ❖ Monitoring vital signs
  - o Pulse Rate (bpm)
  - o Systolic blood pressure (mmHg)
  - o Diastolic blood pressure (mmHg)
  - o Temperature measurements (°C)
- ❖ Electrocardiogram (ECG) (at rest)
  - o Heart Rate (HR) (bpm), PR, QRS, QT, QTcB
- ❖ Clinical Laboratory Assessments
  - o Haematology
    - Ht must be <52%. If Ht level is ≥52%, therapy should be interrupted until the Ht level begins to fall.*
    - Hb must be below 1.15\*Initial Hb (see Figure 1). If Hb is above that level, dosage should be interrupted until the Hb concentration falls back into the range. Then the dosage should be restarted at 2000IU/week of the previous dose.*
  - o Chemistry
  - o Urinalysis
  - o Coagulation

In addition a single non blinded CHDR staff member unconnected to the study will receive reports on the Hb and Ht of the subjects. This individual will be responsible for the dosage adjustments.

Procedure for dosage adjustment:

When the Hb and/or Ht exceeds a certain value (see 5.3) the dose adjustment officer will issue a request for a dosage change for the subject that requires the change. This request will be for the subject that requires the change in treatment but will also be issued to a random placebo subject to preserve the blinding of the study.

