#### 7.2.1 Specific safety assessments

A single non-blinded CHDR staff member unconnected to the study will receive reports on the haemoglobin (Hb) concentration and haematocrit (Ht) of the subjects. This individual will be responsible for the dosage adjustments.

If Ht exceeds 52% in a subject, dosage will be stopped and if necessary,  $\pm 0.5$ L blood will be collected from that subject to correct the Ht percentage to a normal level. This subject will then be excluded from the study.

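### Section 1.4.3 tests the Hb entry limit against the 10–15% target but never tests the Ht entry limit against the 52% stop; for eligible subjects with high baseline Ht the upper part of the target probably lies beyond that stop

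*Protocol*

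**What the plan says.** **Entry.** Section 4.3 (and synopsis section 10) excludes subjects on "Haemoglobin (Hb) concentration $> 9.8$ mmol/l at screening" and on "Haematocrit (Ht) $\geq 48\%$ at screening". Section 1.4.3 repeats both limits.

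**Target.** Section 1.4.3 says: "The rHuEPO treatment in this study will increase Hb levels of the subjects with 10-15" per cent. It justifies the Hb entry limit "because the normal Hb level (11.25 mmol/l) should not be exceeded", and shows 9.8 × 1.15 = 11.27 mmol/l. It gives no corresponding calculation for Ht. Section 6.2 sets the upper bound: "Hb must be below 1.15\*Initial Hb (see Figure 1".

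**Order of the rules.** Section 1.4.1 interrupts dosing at Ht of 52% or more. Below 52%, "the dosage depends on the Hb concentration (see Figure 1".

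**Escalation.** Section 1.4.6, Dosage Rationale, raises the dose from treatment week 5 if Hb is below 1.10 × Initial Hb, "so that it is still possible to reach the target range within 8 weeks". The text states no Ht condition for this other than the 52% rule. Figure 1 is not reproduced in the text available.

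**Consequence at the Ht limit.** Synopsis section 16, section 1.4.1, section 1.4.6 (Stopping criteria) and section 6.2 speak of interruption at 52% or more. Section 7.2.1 says "If Ht exceeds 52% in a subject, dosage will be stopped" and goes on to exclude the subject from the study; section 6.2, Additional safety measures, says the same.

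**The concern.** Hb and Ht largely measure the same thing, so a target set as a percentage rise in Hb implies a similar rise in Ht. The protocol recognises that an entry limit must leave room for the target, and makes the check for Hb. Ht has its own entry limit and its own stop, and the room between them was not checked. A rise from just under 48% to 52% is about 8%, which is less than the bottom of the target.

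Two things are at stake. First, exposure and target attainment in the active arm would depend on baseline Ht, although section 1.4.3 promises the rise without condition. Secondly, if the exclusion wording is followed, losses would fall selectively on active subjects with high baseline Ht, in a trial whose attrition allowance is two per group (22 raised to 24).

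**Working it through.** **1. The protocol's own figure.** 9.8 × 1.15 = 11.27 mmol/l, which reproduces. It is 0.02 above the 11.25 it is meant not to exceed; 11.25 / 1.15 = 9.783.

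**2. The same check for Ht.** Assumption, not stated in the protocol: Ht rises in proportion to Hb (constant MCHC). Then on-treatment Ht = baseline Ht × k, with k = 1.10 to 1.15, and the baseline at which the stop is met is 52 / k.

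- Top of target: 52 / 1.15 = 45.2%
- Bottom of target: 52 / 1.10 = 47.3%

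| Baseline Ht | Ht at +10% | Ht at +15% | Target relative to 52% |
|---|---|---|---|
| 45.0% | 49.5% | 51.75% | wholly below |
| 46.0% | 50.6% | 52.9% | upper part above |
| 47.0% | 51.7% | 54.05% | upper part above |
| 47.5% | 52.25% | 54.6% | wholly above |
| 47.9% | 52.7% | 55.1% | wholly above |

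**3. Cross-check on figures in section 1.4.3.** That section gives professional cyclists' Hb as 8.25–10.25 mmol/l and Ht as 39.2–48.1%. Matching low end to low end and high to high (a construction, since these are two ranges and not paired values) gives ratios of 8.25 / 0.392 = 21.05 and 10.25 / 0.481 = 21.31 mmol/l. For a subject at Hb 9.8:

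- Baseline Ht: 46.0–46.6%
- At +10% (10.78 mmol/l): Ht 50.6–51.2%, below the stop
- At +15% (11.27 mmol/l): Ht 52.9–53.5%, above the stop
- Ht 52% corresponds to Hb 10.94–11.08, a rise of 11.7% to 13.1%

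At these ratios the upper part of the target lies beyond the stop for baseline Hb from about 9.52–9.64 up to 9.8.

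**4. The band in which no part of the target is reachable.** Baseline Ht of 47.3% corresponds to Hb 9.95–10.07 at these ratios, which the Hb limit excludes. An eligible subject in this band needs a ratio of at most 9.8 / 0.4727 = 20.73. The criteria admit one, for example Ht 47.5% with Hb 9.6 (ratio 20.2), but the quoted ranges do not suggest that he is typical.

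**5. Sensitivity to proportionality.** If MCHC changes by a fraction d on treatment, the critical baseline is 52 × (1 + d) / k.

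| MCHC change | Critical baseline at +15% | Critical baseline at +10% |
|---|---|---|
| −3% | 43.9% | 45.9% |
| 0 | 45.2% | 47.3% |
| +3% | 46.6% | 48.7% |

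A conflict stays within the admitted Ht range in all three rows, but its reach varies. At +3% the subject in step 3 just clears the stop at the top of the target (46.56 × 1.15 / 1.03 = 51.99). At −3% he is beyond it even at the bottom (45.99 × 1.10 / 0.97 = 52.2).

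**6. Escalation.** As the text reads, Ht below 52% hands the decision to Hb, and from week 5 Hb below 1.10 × Initial raises the dose. The instruction therefore applies at any Ht below 52%, however close.

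**The case against.** A reader might infer that the entry limit, the target and the stop are mutually incompatible. They are not. Below baseline Ht 45.2% all three fit together, and from 45.2% to 47.3% the lower part of the target is reachable under the stop. The factor 1.15 is a ceiling, not a value each subject must attain. Section 1.4.1 ranks the rules, Ht first and then Hb, so a safety cap that binds before the top of a range is an override and not a contradiction.

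A reader might also infer that the week-5 rule routinely drives subjects towards an unattainable target. Escalation applies only below 1.10 × Initial Hb, so this needs baseline Ht of 47.3% to just under 48%, which at the matched ratios is already excluded on Hb. Figure 1 may also hold a condition that the text omits.

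Other limits are fair. Proportionality is an assumption. The excess of 11.27 over 11.25 is within rounding of the entry limit, since 9.783 rounds to 9.8. Section 7.6 places blood samples before dosing, and Table 1 schedules Hb and Ht before each dose, so a subject found at 52% or more would not be dosed. Section 9.5.2 defines the efficacy set by randomisation, dosing and one post-baseline value, not by target attainment.

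All of this narrows the point. It leaves three things: the missing Ht check, which under proportionality fails for a subject at the Hb entry limit; the unconditional statement of a 10–15% rise; and the two different consequences at the Ht limit, which the ranking in section 1.4.1 does not resolve.

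**Conclusion.** The concern holds as a misalignment in the dosing rationale, together with one textual conflict.

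- Under proportional Hb and Ht, the upper part of the 10–15% target lies at or above the 52% stop for baseline Ht of about 45.2% or more (43.9–46.6% for an MCHC change of −3% to +3%). At the Hb entry limit the stop is met at +11.7% to +13.1%, using the matched cyclist ranges.
- The whole target is beyond the stop only from 47.3% to just under 48%, which the criteria formally admit but the Hb limit largely removes.
- The Hb justification exceeds its own ceiling by 0.02 mmol/l. This is small, but it is printed as the reason for the limit.
- Above 52%, some sections prescribe interruption until Ht falls and others prescribe exclusion. Both cannot apply to the same subject.

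The number of subjects affected cannot be computed, because the protocol gives no Ht distribution for this population. As illustration only, a normal distribution centred on the middle of the cyclist range (43.65%), with that range spanning 3 to 6 SDs, puts roughly a tenth to a quarter of eligible subjects at 45.2% or more. The result depends on whether the Hb limit also caps Ht near 46%. Severity is moderate: it should be settled before dosing, but it does not undermine the comparison of the groups.

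**What to change.** 1. In section 1.4.3, add the calculation for Ht that is made for Hb (entry limit times target, compared with the limit), stating the assumed relation between Hb and Ht.
2. Qualify the statement that treatment will raise Hb by 10–15%, since the Ht rule may bind first.
3. Correct the 9.8 / 11.27 / 11.25 justification so that figure and claim agree.
4. Reconcile the entry limits (synopsis section 10, sections 1.4.3 and 4.3), the target and the week-5 rule (sections 1.4.3, 1.4.6 and 6.2), and the 52% rule, including interruption versus exclusion (synopsis section 16, sections 1.4.1, 1.4.6, 6.2 and 7.2.1). The text should say how the two measures combine when Hb calls for an increase and Ht is close to its limit, or point to where Figure 1 does so. Which limit or rule changes is for the sponsor to decide; none is proposed here.
5. In the report, list for each active subject which limit bound first and whether the Hb target was reached.

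The cost is amendment wording and one extra listing. If an entry limit is moved, the eligible pool may become slightly smaller.
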